**Fig. 2 Fig2:**
[figure not shown]
Trial schema showing an overview of the TEACH-PD trial

### Sample size {14}

A cluster randomized trial with an average cluster size of 37 incident participants over 2 years requires 42 clusters to achieve 80% power to detect a 20% reduction in the hazard of a first PD-related infection with the log-rank test in a cluster-randomized design at a type I error rate of 5%. This translates to approximately 650 events from approximately 1500 participants. The power calculation assumes 53% of the participants in the control group remain infection-free (data derived from HONEYPOT trial [32]) and an intra-cluster correlation coefficient of 0.001. Average cluster size is based on data from eligible Australian and New Zealand PD units in 2014–2015. Sample size calculations were performed using Power Analysis and Sample Size (PASS) Version 15.

### Recruitment and consent {15}

#### Unit recruitment

Eligible PD units (38 units in Australia, 11 units in NZ) will be invited to participate in the trial. Senior managers and clinical staff at each unit will be contacted by investigators and provided a TEACH-PD study synopsis. They will also be invited to attend one of the TEACH-PD virtual preparation sessions which provides additional information such as study background, rationale, and design. PD unit staff are offered opportunities to ask questions and seek further information.

#### Participant recruitment and consent

All patients new to PD requiring training in the participating units and are able to provide informed consent will be invited to take part in the trial. The timing of the initial approach to patients regarding participation will depend on unit practice patterns. This will potentially be made during pre-dialysis education, the first meeting with the PD team, at time of insertion of the PD catheter, at time of flushing of the PD catheter prior to training commencement, or on the first day of starting PD training. Every attempt will be made to approach the patients as early as possible.

All participant information sheets and consent forms (PISCFs) will be approved by an independent Ethics Committee with jurisdiction for the participating site. All participants will provide written informed consent prior to trial participation. If a participant is unable to read the PISCF, an impartial witness will be present during the entire discussion before the participant signs the consent.

## Assignment of interventions: Allocation

### Sequence generation {16a}

Random allocation of clusters will be 1:1 according to a computer-generated randomization algorithm using random permuted blocks within strata formed by country (Australia, New Zealand) and center size (small, medium, large, and very large) to minimize the risks of imbalance in baseline participant and center characteristics across different sized clusters.

### Concealment mechanism {16b}

Allocation will be concealed by holding the stratified random permuted blocks on a password-protected server at the Central Coordinating Center and available only to the trial unblinded statistician.

Due to the type of intervention, allocation is unmasked to the PD nurse trainers and the site contact at the local site.

### Implementation {16c}

All participants at a cluster randomised to an intervention group will receive the intervention, standardized PD training. Participants at a cluster randomised to a control group will receive usual care.

## Assignment of interventions: Blinding

### Who will be blinded {17a}

Emphasis has been placed on ensuring that blinding is maintained. Of the Steering Committee, only one member is unblinded to the details of the intervention and cluster allocation and one member is unblinded to allocation for New Zealand clusters only. Additionally, a minimum number of key operational staff are unblinded to cluster allocations, and all data that are presented are blinded. Unblinded members have received training about the maintenance of blinding in all aspects of the trial conduct.

### Procedure for unblinding if needed {17b}

The Data and Safety Monitoring Board and the independent statistician will make recommendations to the Trial Steering Committee, as required, should safety monitoring warrant unblinding.

## Data collection and management

### Plan for assessment and collection of outcomes {18a, 19}

Participant baseline and outcome data will be captured electronically within the ANZDATA Registry, the New Zealand Peritoneal Dialysis Registry (NZPDR), and a purpose-built REDCap (Research Electronic Data Capture) database according to the country-specific protocol appendices. REDCap [33] is a secure, web-based application designed to support data capture for research studies hosted by the University of Queensland. Original consent forms will be stored locally according to the International Council for Harmonization Good Clinical Practice (ICH GCP) and ethics committee approvals. Investigators will be required to maintain all study documentation, including consent documents, ethics committee approvals, and correspondence, for a period of 15 years after the closure of the trial. The complete participant data set will be made available by the Central Coordinating Center to researchers within the TEACH-PD CRCT study for analysis of sub-studies and country-specific outcomes after the dataset has been locked and analysis for the primary trial outcome is completed. The list of assessments for the participants during the TEACH-PD trial is outlined in Participant study assessments (Table 1).

**Table 1 Tab1:** Participant study assessments

Timing of visit	Pre-training	Post-training (baseline)	Mth 6	Mth 12	Mth 18	Mth 24	End of Study
Screening	X						
Consent, demographics		X					
EQ-5D-5L		X	X	X	X	X	
Exit site infection^a^		X	X	X	X	X	X
Tunnel infection^a^		X	X	X	X	X	X
Peritonitis^a^		X	X	X	X	X	X

^a^Collected in real time as event occurs

### Main study measures {18a}

#### Demographic and clinical information

Participant demographic and clinical data are collected within the ANZDATA and the NZPDR Registries as part of routine Australian and New Zealand clinical practice. Baseline participant data will be extracted from the Registries including age (in years), sex, ethnicity, primary cause of kidney failure, height, weight, co-existing medical conditions (including cardiovascular disease, cerebrovascular disease, peripheral vascular disease, diabetes mellitus, and chronic lung disease), and smoking history. Additional information will be extracted during the enrolment period including kidney failure treatment, peritonitis (undifferentiated between local and systemic cause), tunnel infections and exit site infections, and infection treatment regimens.

#### Quality of life

Quality of life is measured using the EuroQol (EQ-5D-5L, Fig. 3: Example of EQ-5D-5L questionnaire (Australian version)), a widely used instrument developed in Europe which assesses quality of life across five dimensions and five levels at baseline and at each 6-monthly visit. The utility value for estimation of quality adjusted life years (QALYs) will be estimated from the EQ-5D-5L scores using the Australian valuation set [34]. Study questionnaires are collected during participants’ regular clinic visits or e-mailed to participants and completed via REDCap or paper forms.

**Fig. 3 Fig3:**
[figure not shown]
Example of EQ-5D-5L questionnaire (Australian version)

#### Healthcare utilization

Data on healthcare utilization during the trial will be obtained from national- and state-based health databases in Australia and the National Minimum Dataset in New Zealand. Data collected will include prescriptions, ambulatory healthcare encounters, pathology tests, imaging, and all-cause hospitalizations.

The cost of the intervention will be estimated based on patient training time captured using a purpose-built REDCap database in Australia and the NZPDR in New Zealand. Training times for the PD nurse trainers will also be collected and analyzed via the online time usage calculator in the TEACH-PD portal for each nurse trainer.

### Plans to promote participant retention and complete follow-up {18b}

Participant retention will be achieved by several strategies. Participant involvement throughout the trial development, activation and conduct, facilitated primarily by obtaining the Consumer Advisory Board’s input, ensures a patient-centred approach is applied to all trial activities and interactions with trial participants. The study staff at each site will be accessible to participants to answer their questions and respond to any concerns. Practical guidance and suggestions for participant retention awareness training will occur at the site initiation meetings and is documented in the Operations Manual.

For participants who withdraw from the trial, no further information will be collected from the date of withdrawal.

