### Participant timeline {13}

The follow-up period for participants is a minimum of 12 months with a targeted average follow-up period of 2 years (Fig. 2: Trial schema showing an overview of the TEACH-PD trial). Reasons for participant early exit of trial outcomes are kidney transplantation, permanent transfer to hemodialysis, death, transfer to a PD unit not participating in the trial, loss to follow-up, withdrawal of participant consent, or at the patient’s or treating physician’s request.

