### Adverse event reporting and harms {22}

No adverse events (serious or not) will be collected for this study. Trial related outcomes (exit-site infections, tunnel infections, and peritonitis) and deaths will be collected via the Renal Registries.

Incidence of all-cause hospitalisations will be collected via data linkage with national- and state-based health databases. All adverse events will be managed as per usual local clinical care practice.

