A key strength of the TEACH-PD trial is the utilization of a vigorous and adequately powered methodological approach to evaluate a standardized PD training curriculum for both trainers and patients. Both the approach and curriculum have been developed by patients, PD nurses (through THN) [29], doctors and education experts, and have been demonstrated as feasible and acceptable to clinicians and patients [30]. The TEACH-PD trial has a practical focus with broad eligibility criteria, avoidance of extra blood tests, use of local patient care practices, and minimal additional data collection, as data are collected via linkage with national and state-based administrative data and the ANZDATA and NZPD Registries. The registry-based design of the trial offers the advantage of rapid enrolment of eligible participants and complete (and potentially extended) follow-up of all study participants. The investigators acknowledge that PD nurses are the integral aspect of TEACH-PD and the key to its success, such that every effort has been made in designing this study to avoid excessive data collection and management burden. By following a pragmatic design with broad inclusion criteria, patient co-production, and involvement of clinical staff in the research design, the ability to implement the trial’s findings have been maximized [25].

Nonetheless, the TEACH-PD trial also has its limitations. First, it is an open-label trial and therefore potentially introduces detection and performance biases. Second, the trial is limited to PD centers in Australia and New Zealand, such that the findings may not be generalizable to other countries and income settings. TEACH-PD investigators acknowledge and have considered expanding the trial to international sites to improve external validity. Third, there exists a lag time between activation of control and intervention sites due to the time taken to complete the TEACH-PD training curriculum at intervention sites. However, the lengthy follow-up time for both arms will minimize any performance biases. Finally, training practices among sites in the control arm are heterogeneous and may increase outcome variation in the control arm, limiting comparability between arms. In addition, if a TEACH-PD patient from an intervention site is hospitalized and is assisted in their dialysis, this may be performed by a nurse who has not been trained in the TEACH-PD intervention.

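### Withdrawal from the trial ends all data collection, with no option to keep passive registry follow-up of the primary outcome

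*Protocol article*

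**What the plan says.** The operative rule is one sentence in the retention section {18b}: "For participants who withdraw from the trial, no further information will be collected from the date of withdrawal". It makes no exception for registry data and does not grade withdrawal.

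Other sections of the article bear on it:

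- **Source of outcomes.** Adverse event reporting and harms {22}: "Trial related outcomes (exit-site infections, tunnel infections, and peritonitis) and deaths will be collected via the Renal Registries".
- **Other capture route.** The plan for outcome collection {18a, 19} names the two registries and also "a purpose-built REDCap (Research Electronic Data Capture) database according to the country-specific protocol appendices".
- **Routine data.** Under Demographic and clinical information, participant data are "collected within the ANZDATA and the NZPDR Registries as part of routine Australian and New Zealand clinical practice". That sentence concerns demographic and clinical data; infections follow as additional items to be extracted.
- **Consent.** The consent section {26a} says that consent extends to both questionnaires and data linkage, which are distinct activities.
- **Early exit.** Participant timeline {13} lists, among other reasons, "loss to follow-up, withdrawal of participant consent, or at the patient’s or treating physician’s request".
- **Claimed advantage.** The Discussion says that the registry design offers "complete (and potentially extended) follow-up of all study participants".
- **Analysis.** The primary analysis is by intention to treat {20a}. For missing data the article mentions only imputation of randomly missing values, as a sensitivity analysis {20c}.

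**The concern.** The main attraction of a registry-based trial is that outcome ascertainment need not depend on continued active participation. Here it does depend on it: once a person withdraws, the trial stops taking data that the harms section says come through a registry. Table 1 shows the six-monthly EQ-5D-5L as the only recurring item that participants complete themselves. A participant may therefore want to leave trial procedures without objecting to registry use, and the article has no category for that choice.

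The Discussion concedes that the open-label design may bring detection and performance biases. With allocation known at the site, withdrawal could differ by arm and could relate to how dialysis is going. Censoring at withdrawal would then be informative. Recruiting more participants would not remove that bias, and imputing randomly missing values does not address it. Retained registry data would remove it for everyone who agreed to continued follow-up.

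**Working it through.** **1. The passages side by side.** If collection stops at withdrawal {18b}, follow-up cannot be complete for all participants (Discussion). The first is a rule of conduct and the second a claimed advantage, so the claim is the one that needs qualifying. Because {22} names a passive source for every primary-outcome component, part of the loss is avoidable.

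**2. The plan's own sample size.** Inputs from Sample size {14}: HR 0.80, power 80%, type I error 5% (taken as two-sided), average cluster size 37, ICC 0.001, 53% of controls infection-free (taken as at two years).

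- Events (Schoenfeld): 4 × (1.960 + 0.842)² / (ln 0.80)² = 631.
- Design effect: 1 + (37 − 1) × 0.001 = 1.036, so 631 × 1.036 = 654 events.
- Event proportions: control 0.47; intervention 1 − 0.53^0.8 = 0.398; mean 0.434.
- Expected events: 1500 × 0.434 = 651, giving power 79.9%.

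This reproduces the stated figures of about 650 events and 1500 participants. The calculation appears to contain no allowance for withdrawal.

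**3. Non-informative withdrawal (rates assumed).** Infection hazards are λ = −ln(0.53)/2 = 0.317 per year (control) and 0.8 × 0.317 = 0.254 (intervention). If a proportion w withdraws by two years, the withdrawal hazard is ω = −ln(1 − w)/2. The probability of an observed event is λ/(λ + ω) × [1 − exp(−2(λ + ω))].

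| w | Events from 1500 | Power |
|---|---|---|
| 0% | 651 | 79.9% |
| 3% | 642 | 79.3% |
| 5% | 636 | 79.0% |
| 10% | 621 | 78.0% |

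At 3-10% the loss is 9 to 30 events and about 0.5 to 1.9 points of power.

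**4. Informative withdrawal that differs by arm (all inputs assumed).** Take a true HR of 1.00, with 47% two-year risk in each arm. A fraction w are withdrawers with hazard 2h; the rest have hazard h. Solve w(1 − e^(−4h)) + (1 − w)(1 − e^(−2h)) = 0.47. This gives h = 0.3105 at w = 3%, 0.2991 at 8% and 0.2947 at 10%.

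- *Withdrawal spread uniformly over two years.* A withdrawer's chance of an observed event is 1 − (1 − e^(−4h))/(4h), with person-time equal to that divided by 2h. Observed event rates per year are 0.3148 (3%), 0.3107 (8%) and 0.3091 (10%). The ratios are 0.3107/0.3148 = 0.987 and 0.3091/0.3148 = 0.982.
- *Everyone who withdraws does so on day 0.* Only stayers are observed: 0.2991/0.3105 = 0.963 and 0.2947/0.3105 = 0.949.
- *Day 0, with withdrawers at twice the whole-arm average hazard.* Stayers' hazard relative to the average is (1 − 2w)/(1 − w). At 8% v 3%: (0.84/0.92)/(0.94/0.97) = 0.942. At 10% v 3%: (0.80/0.90)/(0.94/0.97) = 0.917.
- *Full follow-up retained:* 1.001, so no material shift.

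If the larger fraction leaves the control arm, the uniform-withdrawal ratios invert to about 1.01 and 1.02. With equal withdrawal in both arms there is no shift in this model.

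**5. Cross-check with a treatment effect.** A simulation set the hazard ratio within withdrawers and within stayers at 0.80, gave withdrawers twice the hazard, and spread withdrawal uniformly. With 2% control and 10% intervention withdrawal, the event-rate ratio is 0.831 when censored and 0.851 with full follow-up. With 10% and 2% it is 0.771 and 0.755. Each is a shift of about 2%.

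**The case against.** **Consent law and unseen documents.** A participant who withdraws consent to data use must be allowed to end collection, and tiers of withdrawal often sit in the consent form, Operations Manual or country appendices, none of which is shown. The first point stands and limits what is avoidable. The second does not remove the finding, because the article does more than omit a detail: it states a rule for everyone who withdraws from the trial.

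**Intention to treat.** A reader might infer that the rule breaks it. The article does not support that. Data up to withdrawal are kept, and nothing removes the participant from the randomized arm. The issue is censoring that may be informative, which is narrower.

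**Questionnaires.** A reader might also infer that anyone who stops the EQ-5D-5L is thereby lost for the primary outcome. No section says that declining questionnaires counts as withdrawal, and {13} lists consent withdrawal apart from exit at the patient's or physician's request. What stands is that the article offers no defined intermediate status.

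**Data already held.** It is tempting to say that the data exist for every component at no cost. REDCap is a named capture route, and the wording on routine practice is not attached to infections, so this is not established. The harms section still names the registries for all three components.

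**The Discussion claim.** It describes an advantage and is not an operating rule, and {13} openly lists losses. That makes it loose wording, which a short qualification corrects.

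**Timing.** All 42 clusters were randomized and recruitment was due to end by June 2023. Follow-up lasts at least 12 months per participant, so a choice offered at the point of withdrawal would still apply to later withdrawals.

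**Conclusion.** The point holds as a design choice worth changing. The single withdrawal rule allows avoidable and possibly informative censoring of the primary outcome, and it does not fit the claim of complete follow-up.

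The effect on precision is small: at most about 2 points of power for assumed withdrawal of up to 10%. The possible bias is modest: about 1-2% on the hazard ratio if withdrawal differs between arms (8% or 10% v 3%), withdrawers carry twice the hazard and exits are spread over two years. About 4-8% is reached only with withdrawal at the very start, and its upper end also needs withdrawers at twice the whole-arm average hazard. A reader might take that upper end as the expected bias; nothing in the article supports it.

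The direction depends on which arm loses more people. No withdrawal rate, difference between arms or hazard multiple is given, so these figures are illustrations and not estimates. They also rest on constant hazards and on reading the 53% as a two-year figure.

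**What to change.** In {18b}, and subject to ethics approval, define two levels:

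- **(a)** Questionnaires and trial contact stop, while registry and linkage follow-up continue where the participant agrees.
- **(b)** Full withdrawal of consent to data use, with no further data from that date.

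Offer (a) at the point of withdrawal, with (b) always available. Record the level, date and reason by arm. Censor for withdrawal only at (b), and leave the other censoring reasons in {13} unchanged. Qualify the Discussion statement on complete follow-up to except full withdrawals.

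The cost is a small amendment to the protocol and consent material with ethics approval, and possibly fresh agreement from those already enrolled. No visits or staff are added. For any outcome component captured through REDCap rather than a registry, the trial should check whether passive capture under (a) is feasible.

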### Confidentiality {27}

Participants’ records and the data generated by the study will remain confidential in line with the recommendations of the National Health and Medical Research Council (NHMRC), the 2001 privacy legislation in Australia, and the Privacy Act 2020 in New Zealand. Any information that may identify a participant will be excluded from data presented in the public arena. Data will be stored in a secure, lockable location. Electronic data storage will have adequate password protection. The participants in this study will be identified only by initials and study number. De-identified information will only be released to the Central Coordinating Center or designee, according to ethics committees’ approval.

### Plans for collection, laboratory evaluation, and storage of biological specimens for genetic or molecular analysis in this trial/future use {33}

No additional biological samples outside those collected as part of routine clinical care are being collected from participants.

## Statistical methods

### Statistical methods for primary and secondary outcomes {20a}

Data will be analyzed at the patient level. Patient and treatment characteristics will be presented by study group using descriptive statistics. The primary outcome (coded as yes/no) and follow-up time (censored if < 24 months) will be displayed using Kaplan–Meier survival curves by group and by center size. Survival estimates of the treatment groups will be compared using the log-rank test for clustered data. Cox regression models with standard errors to allow for non-independent observations due to clustering will be used to assess the effect of the intervention on the primary and secondary outcomes. The models will be adjusted for cluster size category and country. The proportional-hazards assumption will be tested for each model. All data will be analyzed on an intention-to-treat basis with *p*-values less than 0.05 taken to indicate statistical significance.

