### Outcomes {12}

#### Primary outcome

The primary outcome is time from the first day of PD training to the first occurrence of any PD-related infection (PD peritonitis, tunnel infection, or exit site infection), as defined by ISPD guidelines [28].

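### The planned Kaplan–Meier display, read as risk, overstates the probability of PD-related infection in both arms because death, transplant and permanent hemodialysis transfer are treated as ordinary censoring

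*Protocol article*

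**What the plan says.** The primary outcome (Outcomes {12}) is "time from the first day of PD training to the first occurrence of any PD-related infection". Death, transplantation and transfer to hemodialysis are not components of it.

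The participant timeline {13} states: "Reasons for participant early exit of trial outcomes are kidney transplantation, permanent transfer to hemodialysis, death". The same list goes on to transfer to a non-participating PD unit, loss to follow-up, withdrawal of consent, and the request of the patient or treating physician.

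The statistical methods {20a} use one rule for follow-up time, whatever the reason for exit: "The primary outcome (coded as yes/no) and follow-up time (censored if < 24 months". The outcome is then shown with "Kaplan–Meier survival curves by group and by center size". For inference, "Survival estimates of the treatment groups will be compared using the log-rank test for clustered data", and the intervention effect is estimated with "Cox regression models with standard errors to allow for non-independent observations due to clustering". The article names no cumulative incidence or other competing-risk method.

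**The concern.** Kaplan–Meier treats a censored participant as still at risk and likely to have the event at the same rate as those who remain. That is tenable for someone who moves to a non-participating unit and stays on PD. It is not tenable for someone who has died, been transplanted or left PD permanently, because no first PD infection can then follow within the trial. With those exits censored, one minus Kaplan–Meier estimates infection risk in a hypothetical setting where nobody leaves PD by these routes.

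The stake is the absolute scale. Readers commonly take risks and risk differences from curves of this kind. The trial is pragmatic and includes a cost-effectiveness analysis from the health funder's perspective, for which the relevant figure is the risk that occurs in practice. Hemodialysis transfer and death are also secondary outcomes, so the exits may differ between arms, and the planned curves could not show it.

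**Working it through.** **The plan's own figures.** The sample size section {14} gives a control infection-free proportion of 53%, a 20% hazard reduction, an ICC of 0.001, 42 clusters averaging 37, and about 650 events from about 1500 participants.
- Intervention infection-free proportion: 0.53^0.8 = 0.602.
- Mean event probability: 1 − (0.53 + 0.602)/2 = 0.434, so 1500 × 0.434 = 651 events.
- Schoenfeld's formula (two-sided 5%, 80% power, HR 0.80) gives 631 events. With design effect 1 + 36 × 0.001 = 1.036, 631 × 1.036 = 654.

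The stated design reproduces.

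**Assumptions for the comparison.** The article gives no time point for the 53% and no rate for death, transplant or permanent transfer. I take 53% as net infection-free survival at 24 months and constant hazards. I vary the combined exit hazard μ from 0.10 to 0.35 per year, at first equal in both arms.

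**Formulas.** Control infection hazard λ = −ln(0.53)/2 = 0.317 per year; intervention 0.8λ = 0.254 per year.
- One minus Kaplan–Meier at 2 years: 1 − exp(−2λ), whatever μ is. Control 47.0%, intervention 39.8%, difference 7.2 points, number needed to train 1/0.0718 = 13.9.
- Cumulative incidence at 2 years: λ/(λ+μ) × [1 − exp(−2(λ+μ))], with 0.8λ in the intervention arm.

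Worked case, μ = 0.25: control 0.317/0.567 × (1 − exp(−1.135)) = 38.0%; intervention 0.254/0.504 × (1 − exp(−1.008)) = 32.0%; difference 6.0 points.

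| μ per year | Control | Intervention | Difference (points) | Number needed to train | Kaplan–Meier difference too large by |
|---|---|---|---|---|---|
| Kaplan–Meier | 47.0% | 39.8% | 7.2 | 13.9 | – |
| 0.10 | 43.0% | 36.4% | 6.6 | 15.0 | 8% |
| 0.25 | 38.0% | 32.0% | 6.0 | 16.8 | 20% |
| 0.35 | 35.0% | 29.5% | 5.6 | 18.0 | 29% |

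Risks and the difference are overstated; the number needed to train is understated.

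**Unequal exits.** Set the control 24-month exit risk at 30% (μ = −ln(0.70)/2 = 0.178 per year) and vary the intervention/control exit hazard ratio. The cumulative incidence difference is 5.2 points at a ratio of 0.8, 6.3 at 1.0, 7.3 at 1.2 and 8.3 at 1.4, against 7.2 by Kaplan–Meier. The two agree at a ratio of about 1.18. Solving the same equation at μ = 0.10, 0.25 and 0.35 gives 1.17, 1.19 and 1.20. Above that ratio Kaplan–Meier understates the absolute difference.

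**Other reading of the 53%.** If 47% is instead the crude proportion infected, then over 24-month exit risks of 10% to 40% control one minus Kaplan–Meier is 49.2% to 57.9%, and the difference is 7.4 to 8.0 points against 7.1 to 6.7 by cumulative incidence. The direction is the same.

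**The case against.** **The inference is on the hazard.** The objective is delay of the first infection, the trial is powered on a hazard reduction, and Kaplan–Meier curves that censor these exits are the usual companion to a log-rank test and a cause-specific Cox model. This stands. A reader might infer that the primary analysis is biased; the article does not support that, because censoring competing exits is the correct handling for the cause-specific hazard.

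**The benefit may not be exaggerated.** A reader might infer that the curves must overstate the absolute benefit. They need not: the overstatement disappears at an exit hazard ratio near 1.18 and reverses above it. Only the overstatement of risk within each arm is unconditional once such exits occur.

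**No absolute risk is promised.** The article plans a display. It does not announce a 24-month risk, a risk difference or a number needed to train. This also stands: the error arises when the curves are read or reported as risk.

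**The analysis plan may add cumulative incidence curves.** It may, and it is not shown. But {20a} does not leave the estimator open. It names Kaplan–Meier and a single censoring rule, so the point concerns a stated choice.

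**The size is assumed.** No exit rate is given. Over 24-month exit risks of 10% to 40%, with equal exits, the difference is inflated by only 0.3 to 1.2 points. The modest size is conceded. The overstatement of control risk over that range is larger, 2.1 to 9.2 points.

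**Conclusion.** The point holds as one about the display of infection risk. Given {13} and {20a} as written, one minus Kaplan–Meier exceeds the actual probability of a first infection in both arms. Under the stated assumptions (constant hazards, 53% as net 24-month survival, HR 0.80, equal exit hazards of 0.10 to 0.35 per year), it exceeds control risk by 4 to 12 points and the risk difference by 0.5 to 1.6 points. The effect on the difference is conditional: it reverses if exits are about 1.2 times as frequent, or more, in the intervention arm. Hemodialysis transfer that follows a first infection comes after the event and plays no part. The clustered log-rank test, the Cox hazard ratio and the sample size are unaffected. This is a worthwhile and cheap improvement, not a correction of the primary inference.

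**What to change.** In {20a}, make Aalen–Johansen cumulative incidence curves, by arm and by center size, the display of infection risk. Kaplan–Meier curves may stay as the companion to the log-rank test, labelled as net of competing exits. Classify every exit listed in {13}:
- Competing events: death, kidney transplantation and permanent hemodialysis transfer before a first infection.
- Censoring: withdrawal of consent, loss to follow-up, transfer to a non-participating PD unit, exit at patient or physician request while still on PD, and administrative end of follow-up.

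Take any reported 24-month risk or risk difference from the cumulative incidence curves, with an interval that allows for clustering. Leave the log-rank test and the Cox model as they are.

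The cost is one extra analysis routine. The exit reasons are already defined in {13}, and deaths and kidney failure treatment already come from the registries. The displayed absolute benefit may come out slightly smaller.
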